## Abstract

**Introduction:**

Immunoglobulin A (IgA) nephropathy is a disease that presents with urinary symptoms such as glomerular hematuria and urinary protein positivity, with predominant deposition of IgA in the mesangial region of the glomerulus. Corticosteroids are mainly used for treatment; however, infection is a serious adverse event, and evidence regarding therapeutic efficacy is insufficient, thus new treatments are strongly desired. Mesenchymal stem cells (MSCs) contribute to the amelioration of inflammation and recovery of organ function in inflammatory environments by converting the character of leukocytes from inflammatory to anti-inflammatory and inducing the proliferation and differentiation of organ component cells, respectively. These properties of MSCs have led to their clinical application in various inflammatory diseases, but this study is the first clinical trial of MSCs for refractory glomerulonephritis in the world. This study is registered and assigned the number, jRCT2043200002 and NCT04342325.

**Methods:**

This will be a phase 1, open-label, multiple-center, dose-escalation study of adult patients with refractory IgA nephropathy resistant to or difficult to treat with existing therapies. ADR-001 will be administered intravenously to from three to six patients at a dose of 1 × 10^8^ cells once in the first cohort and to six patients twice at 2-week intervals in the second cohort, and observation will continue until 52 weeks. The primary endpoint will be the evaluation of adverse events up to 6 weeks after the start of ADR-001 administration. Secondary endpoints will be the respective percentages of patients with adverse events, clinical remission, partial remission, remission of urine protein, remission of hematuria, time to remission, changes in urine protein, hematuria, and estimated glomerular filtration rate.

**Results:**

Following the administration of ADR-001 to patients with IgA nephropathy, the respective percentages of patients with adverse events, asymptomatic pulmonary emboli, clinical remission, partial remission, urine protein remission, hematuria remission, their time to remission, changes in urine protein, hematuria, and glomerular filtration rate will be determined.

**Conclusion:**

This study will evaluate the safety and tolerability of ADR-001 and confirm its therapeutic efficacy in adult patients with refractory IgA nephropathy.

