Adipose-derived mesenchymal stem cells have been shown to reduce serum creatinine concentration, BUN, and kidney weight in a rat model of anti-glomerular basement membrane nephritis in non-clinical studies (7). On the other hand, there is no appropriate animal model of IgA nephropathy. However, from the pathogenesis of IgA nephropathy (J Am Soc Nephrol. 2011 Oct;22 (10):1795-803.) and previous reports that MSCs are effective not only in cellular immunity but also in humoral immunity, such as suppression of antibody production (7–9), we believe that MSCs may be effective in IgA nephropathy. Considering clinical application, more than 1,000 clinical trials using MSCs have been conducted worldwide (5), and more than 30 clinical trials have been conducted in the field of nephrology transplantation, CKD, AKI, diabetic kidney disease, and focal segmental glomerulosclerosis. Some promising results have been observed, such as the administration of ASCs for renal artery stenosis (10). However, clinical studies of ASCs in CKD have been limited to case reports, and therapeutic potentials of administered allogeneic ASCs in patients with therapy-resistant nephritis have not been clearly reported (11). Therefore, it is eagerly awaited to clarify this. In this study, we will conduct a prospective clinical trial to evaluate the safety and tolerability of one and two intravenous doses of ADR-001, allogeneic ASCs, as a primary endpoint and to confirm therapeutic efficacy as a secondary endpoint in patients with refractory IgA nephropathy who are resistant to or difficult to manage with existing therapies.

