## Method and Design

### Design

This will be an open-label, multiple-center, dose-escalation study of adult patients with refractory IgA nephropathy who are resistant to or difficult to manage with existing therapies. Figure 1 shows an outline of the study. ADR-001 will be administered intravenously at a dose of 1 × 10^8^ cells once in the first cohort and twice at 2-week intervals in the second cohort, and evaluation and observation will continue until 52 weeks. Supplementary Figure 1 presents the schedule of the study. To conduct a safe trial, the protocol was designed so that the first cohort of single-dose patients will be completed before proceeding to the second cohort of double-dose patients. A maximum of 12 subjects will be enrolled from the Nagoya University Hospital and Kasugai Municipal Hospital. The main analysis population will be the safety analysis population for the analysis of the primary endpoint and the largest analysis population full analysis set (FAS) for the analysis of the secondary endpoint. Analysis will also be conducted on the analysis population conforming to the study protocol Per Protocol Set (PPS) to confirm the robustness of the analysis results. The trial will be conducted in compliance with the Declaration of Helsinki and Japan’s Ministerial Ordinance on Good Clinical Practice for Cellular and Tissu-based Products.

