
### Screening Process

After obtaining consent, the following tests and observations will be performed or confirmed before registration:

1.Confirmation of subject eligibility based on inclusion/exclusion criteria.2.Background check on the subject (date of birth, sex, weight, and height).3.Status of primary disease (duration of IgA nephropathy and historical eGFR) and previous treatment (type and duration of drug therapy, lifestyle, and dietary guidance for IgA nephropathy).4.Confirmation of medical history and complications (clinically significant diseases within the past 6 months).5.Vital signs (systolic blood pressure, diastolic blood pressure, heart rate, and body temperature).6.Oxygen saturation.7.Clinical examination.8.Check for concomitant medications and concomitant therapy.9.Simple CT scan of the area between the chest and pelvic region.10.Echocardiography and electrocardiography.

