#### Sample Size

The target number of patients will be three to six in the first cohort and six in the second cohort, for a total of 9–12.

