#### Data Analysis Plan

The main analysis population will be the safety analysis population for the analysis of the primary endpoint and the largest analysis population (FAS) for the analysis of the secondary endpoint. Analysis will also be conducted on the analysis population conforming to this study protocol (PPS) to confirm the robustness of the analysis results. Adverse events, which are the primary and safety endpoints, will be classified and aggregated using CTCAE v5.0/MedDRA/J v22.1, and incidence rates and 95% confidence intervals will be calculated. In addition, the incidence rates will be calculated for each of the following categories: cohort, organ major classification, preferred term, severity, and association with ADR-001. As the secondary endpoint, we will calculate the percentage and 95% confidence interval and estimate each of the following parameters using the Kaplan–Meier method: patients who achieve clinical remission, partial remission, urinary protein remission, hematuria remission, and time to remission. Summary statistics (mean, standard deviation, etc.) will be calculated for urine protein, hematuria, and eGFR. For safety assessment endpoints such as vital signs and clinical laboratory values, summary statistics (mean, standard deviation, etc.) will be calculated, and their transition will be shown.

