This will be the first clinical trial of MSCs in patients with refractory IgA nephropathy, and positive therapeutic outcomes are expected. In animal experiments, MSCs were shown to be effective against highly inflammatory nephritis (7). After MSCs are administered, they enter the bloodstream and secrete various inflammation-regulating cytokines to control local inflammation when they reach the local inflammatory area. Therefore, while inflammation is locally controlled, systemic side effects are unlikely to occur. In other words, MSCs are expected to have improved therapeutic effects and limited side effects, such as infections caused by steroids and immunosuppressive drugs. Our study also suggests that MSCs do not cause excessive immunosuppression (17). However, a possible side effect is that the cell mass itself and a subsequent blood clot can induce pulmonary embolism. We are planning to prevent potential pulmonary embolism as much as possible by using heparin in combination with ADR-001. Although bleeding tendency needs to be taken into account, we set a clinically acceptable heparin dose based on the one used during extracorporeal circulation for hemodialysis. Concerns about pulmonary embolism also increase with the number of cells administered; however, in our trial, the number of cells administered will be based on past administration for other diseases and will not particularly be high. In addition, ECG and SpO_2_ monitors will be worn during administration, and ECG, laboratory tests, such as d-dimer, and echocardiography will be performed on the day of administration and the following day to detect early signs of right ventricular strain and pulmonary embolism. The transplantation of induced pluripotent stem cells, a primitive stem cell, has raised concerns about the occurrence of teratomas in animal experiments. Since MSCs do not proliferate indefinitely, there is little concern about the development of malignant tumors; however, to guarantee safety, CT scans will be performed to check for malignant tumors of the whole body at 52 weeks. Furthermore, patients who present with concerns regarding malignancy prior to the administration of ADR-001 will not be included in the study. The number of doses will be one for the first cohort and two for the second cohort. Based on our results from animal models, we expect that the more times ADR-001 is administered, the more effective the treatment will be. However, since the main purpose of this study is to confirm safety, and since this will be the world’s first study on nephritis, we decided to prioritize safety and start the study with a single dose. In addition, the first cohort will include a population with good renal function for safety reasons. The second cohort will include patients with a wide range of renal functions. Based on the results of this study, we will determine the level of renal function that is best suited for treatment with ADR-001 in terms of safety and efficacy.

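### The article says the study will confirm efficacy and identify the best-suited renal function, but 9–12 uncontrolled patients selected on screening proteinuria can only explore either question

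*Protocol article*

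**What the plan says.** The abstract's Conclusion states that the study will evaluate safety and tolerability and "confirm its therapeutic efficacy in adult patients with refractory IgA nephropathy". The last paragraph of the Introduction gives the same aim: "to confirm therapeutic efficacy as a secondary endpoint in patients with refractory IgA nephropathy".

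The Design section reads "This will be an open-label, multiple-center, dose-escalation study of adult patients with refractory IgA nephropathy", and the Sample Size section sets "three to six in the first cohort and six in the second cohort, for a total of 9–12". Every patient receives ADR-001: one dose in the first cohort, two in the second. No efficacy hypothesis, comparator or reference remission rate is given.

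Under Inclusion Criteria, patients qualify on urine protein at screening: above 0.5 g/gCr for the first cohort, with further bands of urine protein and eGFR added for the second. Study Endpoints lists changes in urine protein, hematuria and eGFR among the secondary endpoints, and counts remission only when its criteria are met at three consecutive assessments.

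For the remission endpoints the Data Analysis Plan will "calculate the percentage and 95% confidence interval and estimate each of the following parameters using the Kaplan–Meier method". For the continuous ones it says "Summary statistics (mean, standard deviation, etc.) will be calculated for urine protein, hematuria, and eGFR".

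The Discussion says the results will be used to determine which level of renal function is best suited to ADR-001 for safety and efficacy. Its closing paragraph names two limitations: restricted increases of steroids and RAS inhibitors, and the exclusion of patients with more severely impaired renal function.

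**The concern.** Confirming efficacy means attributing an improvement to the drug with stated control of error. That needs a comparator, or at least a justified reference rate and a decision rule. The article has none of these, and an analysis plan that is not shown could not supply a control group.

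There is also a built-in bias in the favourable direction. Patients admitted because one urine protein reading exceeded a cut-off will, on average, read lower next time even if nothing is done. Without a control, that fall cannot be told apart from a drug effect.

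The renal-function statement asks still more: a comparison of efficacy between subgroups of the same few patients. At stake is a published conclusion that efficacy was confirmed, or a renal-function range chosen for later trials, on data that cannot bear it.

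**Working it through.** **1. The plan's own figure.** 3 + 6 = 9 and 6 + 6 = 12, so the stated total of 9–12 reproduces. No alpha, power, effect size, SD or null rate is given, so there is no efficacy calculation to check.

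**2. Precision of a remission percentage.** Clopper–Pearson 95% limits for x of n are the 2.5% point of Beta(x, n−x+1) and the 97.5% point of Beta(x+1, n−x):

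- 3/6: 12% to 88%
- 2/6: 4% to 78%
- 3/9: 7% to 70%
- 6/12: 21% to 79%
- 0/12: 0% to 26%

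For a mean change, the 95% half-width is t(0.975, n−1)/√n, in units of the SD of the change: 1.05 at n = 6, 0.77 at n = 9 and 0.64 at n = 12.

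**3. Dependence on a reference rate.** Take 12 patients and an exact one-sided rule at no more than 2.5%. If untreated remission is *assumed* to be 10%, five remissions are needed, and power is 56% at a true 40%. If it is *assumed* to be 5%, three are needed and power is 92%. If it is *assumed* to be 20%, six are needed and power is 34%. The same data could be convincing or not, depending on a rate the article does not state.

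**4. Regression to the mean in urine protein.** Let log urine protein have between-patient SD b and within-patient SD w in a source population with median m, and let entry require a reading above c. With no drug effect, the expected log fall at the next reading is

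w²/√(b²+w²) × φ(z)/(1−Φ(z)), where z = ln(c/m)/√(b²+w²).

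The documents give no variability, so m = 0.7 g/gCr, b = 0.4–0.6 and w = 0.2–0.4 are *assumptions*; c = 0.5 comes from the Inclusion Criteria. For b = 0.5, w = 0.3:

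- √(0.25+0.09) = 0.583
- z = −0.336/0.583 = −0.577
- φ/(1−Φ) = 0.338/0.718 = 0.470
- log fall = 0.09/0.583 × 0.470 = 0.073, a 7% fall in the geometric mean

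Over the assumed range the fall is 3% (b = 0.6, w = 0.2) to 12% (b = w = 0.4). A wider set of assumptions (m 0.5–1.2, b 0.5–0.7, w 0.2–0.4) gives 1–18% for entry above 0.5 and 3–33% for entry above 1.0 g/gCr.

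**5. Effect of averaging the baseline.** If baseline is the mean log of the qualifying value and one further independent pre-dose value, the expected log fall halves. In the example it goes from 0.073 to 0.036, or from 7% to about 4%. It does not vanish.

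**6. Renal-function comparison.** The first cohort admits only patients with eGFR above 60. All patients at or below 60 therefore come from the second cohort, number at most six, and all are assigned two doses. Renal function is thus partly confounded with number of doses. Selection on eGFR adds an artefact whose sign depends on the band. With *assumed* within-patient SD 4–8, between-patient SD 20 and source mean 60–80, it is −0.2 to −2.4 mL/min/1.73 m² for entry above 60, and +0.6 to +4.3 for entry between 20 and 60.

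**The case against.** The strongest reply is that the article uses *confirm* loosely. The Discussion says "since the main purpose of this study is to confirm safety", efficacy is only secondary, and the Data Analysis Plan is descriptive with no efficacy test. That is right about the operative plan: a reader should not infer that a formal confirmatory test is intended. But the aim is stated in two places, the renal-function statement is firmer still, and the limitations do not correct either.

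Safeguards also exist. Background treatment is in principle held stable from 3 months before consent, persistent proteinuria is the stated target, and remission needs three consecutive assessments. Under the assumptions of step 4, 9–19% of untreated patients would read below 0.5 g/gCr at the next visit, but only about 5–10% would do so at any three consecutive of the seven visits. (0.5 is the entry cut-off; the article gives no remission threshold.) So the rule lessens the problem for remission. It does nothing for the change endpoints.

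Three stronger readings are tempting and are not supported:

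- *The historical eGFR collected at screening would separate drug effect from regression to the mean.* Past eGFR says nothing about regression in urine protein, and it is not the only own-control, since baseline values exist. The article lists "duration of IgA nephropathy and historical eGFR" as disease background and does not say how many values there are.
- *The plan discards within-patient pairing.* The sentence on summary statistics ends its list with *etc.* and does not exclude change from baseline.
- *Visit means make the estimate far less precise.* For n = 6, a true 30% fall, within-patient log-SD 0.3 and between-patient log-SD 0.5–0.7 (all assumed), the sampling SD of the ratio of visit means is 0.14–0.15. For the geometric mean ratio it is 0.7 × 0.3 × √2/√6 = 0.12. The gain is modest.

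Detailed models for eGFR and hematuria belong to an analysis plan that is not shown, and their absence here is no fault.

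**Conclusion.** The point holds as one about claims and stated limitations, with a modest recommendation on analysis. An uncontrolled study of 9–12 patients with no efficacy hypothesis, comparator or reference rate cannot confirm efficacy or establish the best-suited renal function. The interval widths follow from the sample size alone. The direction of the urine protein bias follows from entry above a threshold; its size, roughly 3–12% for entry above 0.5 g/gCr, rests wholly on assumed variability and could be smaller or larger. The article's limitations mention none of this.

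The change endpoint and the summary-statistics sentence are not contradictory, but the sentence does not name change. For a typically skewed measure such as urine protein, a within-patient ratio fits that endpoint better than a mean and SD. The primary safety objective is untouched. The correction is worth making and is not critical.

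**What to change.** - In the abstract's Conclusion and at the end of the Introduction, replace *confirm* with *explore* or *describe preliminary* efficacy.
- In the Discussion, say that results by renal function will be described to inform later studies, not that the best-suited level will be determined.
- Add three limitations: no control group, small sample, and regression to the mean from entry on a screening threshold.
- In the Data Analysis Plan, state that urine protein will be reported as the within-patient ratio to baseline: geometric mean ratio with 95% confidence interval, plus individual profiles. Define baseline as the mean of the available pre-dose values, not the qualifying screening value alone. This lessens regression to the mean but does not remove it.
- Optionally, describe eGFR slope before and after dosing if enough historical values exist, labelled descriptive.

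No patients, visits or tests are added. The cost is a weaker efficacy claim and a little extra output.

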## Introduction

Immunoglobulin A (IgA) nephropathy presents with urinary findings suggestive of nephritis, such as glomerular hematuria and positive urinary protein. It is characterized by predominant IgA deposition in the glomeruli.

Many cases are detected as asymptomatic urine analysis abnormalities; however, in some cases, the kidney damage progresses without a noticeable onset of the disease, with the disorder being detected by a hypertension diagnosis or blood test abnormalities such as blood urea nitrogen (BUN) and serum creatinine levels. In addition, although rare, edema due to acute nephritis or nephrotic syndrome may trigger detection, including gross hematuria associated with acute upper respiratory infection, mainly tonsillitis or pharyngitis. For a definitive diagnosis, it is necessary to show that IgA is deposited mainly in the mesangial region of the glomeruli by renal biopsy. Currently, adult patients with IgA nephropathy are treated with blood pressure management, lifestyle modification, and maximally tolerated dose of renin-angiotensin system (RAS) inhibitors. Further, corticosteroids and immunosuppressive drugs are used for patients at high risk of progressive kidney disease despite the above treatments. In some Asian countries, palatine tonsillectomy (plus steroid pulse therapy), antiplatelet drugs, and n-3 fatty acids (fish oils) are also used (1). Treatment with corticosteroids is the gold standard for IgA nephropathy with high risk of disease progression, but there is no established treatment regimen for patients who are refractory to steroid therapy. In particular, in Japan, tonsillectomy is performed together with steroid therapy to enhance the therapeutic effect; however, the level of evidence to support this is currently not significant. Recently, two clinical trials have been reported (2, 3). First, as for the STOP-IgA trial, it failed to demonstrate statistical efficacy in preventing the progression of kidney dysfunction and showed high risk of severe infectious disease (2). Second, as for the TESTING trial, steroid therapy showed statistical efficacy in preventing the progression of kidney dysfunction, but adverse events such as infections led to early discontinuation of the trial (3). Therefore, there is a critical need for immunosuppressive therapy for treatment-resistant IgA nephropathy that does not increase side effects. Owing to this, we hypothesized mesenchymal stem cells (MSCs) as a new treatment approach because of their therapeutic properties.

Mesenchymal stem cells have shown beneficial effects in a broad range of animal disease models by promoting regeneration and/or enhancing immunoregulatory effects. Cell therapy for kidney disease using MSCs began with a report of bone marrow-derived mesenchymal stem cell (BM-MSC) administration in a mouse model of cisplatin nephropathy (4). Since then, a number of studies have reported the therapeutic effects of BM-MSCs in acute kidney injury (AKI), nephritis, and chronic kidney disease (CKD) models, demonstrating that MSCs have a renal protective effect. MSCs have been clinically applied to various diseases, especially those that are difficult to treat with currently existing immunosuppressive drugs. Based on our research findings, we recognized the therapeutic properties that could be harnessed from MSCs, viz. strong anti-inflammation properties and their ability not to induce harmful immunosuppression even in excessive amounts. In addition to the previously mentioned immunosuppressive effects, MSCs have a negative HLA-DR and are not prone to rejection, making it possible to perform an allotransplant in which someone else’s MSCs are administered even when the blood type or HLA is incompatible. For these reasons, MSCs have been tested in clinical trials for a variety of inflammatory diseases, including renal disorders (5). Adipose-derived mesenchymal stem cells (ASCs) have a higher regenerative capacity than BM-MSCs because they secrete more growth factors such as hepatocyte growth factor and vascular endothelial growth factor. They also secrete more immunomodulatory factors and have been reported to have a high immunomodulatory function (6, 7). Furthermore, the physical and mental hurdles for donors are low because fat is relatively safe and easy to harvest. In culture, ASCs have excellent proliferative capacity and efficient culture techniques have been established, making it is possible attain the number of cells required for therapy in a relatively short period of time. Therefore, ASCs have many advantages over other cells and are considered to have high feasibility and therapeutic efficacy in clinical applications.

Adipose-derived mesenchymal stem cells have been shown to reduce serum creatinine concentration, BUN, and kidney weight in a rat model of anti-glomerular basement membrane nephritis in non-clinical studies (7). On the other hand, there is no appropriate animal model of IgA nephropathy. However, from the pathogenesis of IgA nephropathy (J Am Soc Nephrol. 2011 Oct;22 (10):1795-803.) and previous reports that MSCs are effective not only in cellular immunity but also in humoral immunity, such as suppression of antibody production (7–9), we believe that MSCs may be effective in IgA nephropathy. Considering clinical application, more than 1,000 clinical trials using MSCs have been conducted worldwide (5), and more than 30 clinical trials have been conducted in the field of nephrology transplantation, CKD, AKI, diabetic kidney disease, and focal segmental glomerulosclerosis. Some promising results have been observed, such as the administration of ASCs for renal artery stenosis (10). However, clinical studies of ASCs in CKD have been limited to case reports, and therapeutic potentials of administered allogeneic ASCs in patients with therapy-resistant nephritis have not been clearly reported (11). Therefore, it is eagerly awaited to clarify this. In this study, we will conduct a prospective clinical trial to evaluate the safety and tolerability of one and two intravenous doses of ADR-001, allogeneic ASCs, as a primary endpoint and to confirm therapeutic efficacy as a secondary endpoint in patients with refractory IgA nephropathy who are resistant to or difficult to manage with existing therapies.

